**Figure 2 F2:**
[figure not shown]
IVORY trial visits—timeline and assessments. ECHO, echocardiogram; ^18^F-FDG, 2-deoxy-2-[fluorine-18] fluoro-D-glucose; IMP, investigational medical product; PET, positron emission tomography.

During the maintenance phase (V8–V14), participants will be dosed once weekly. These visits will last for 1–1.5 hours. They will be similar to the induction phase visits; however, administration of the IMP will only occur once safety bloods taken during the visit are checked. Cardiac biomarkers and lymphocyte subsets will be measured during alternate maintenance visits (V8, V10, V12, V14). Within approximately 1 week from the completion of dosing, a second postdose ^18^F-FDG PET/CT scan will be undertaken. The final encounter will take place approximately 4 weeks after the final dosing visit via telephone unless an in-person visit is necessary for clinical or safety reasons.

Patients will be withdrawn from the trial after recruitment if any of the prespecified general, cardiac, renal or liver withdrawal criteria are met. They will also be withdrawn from the trial if they are positive for COVID-19 during dosing. The withdrawal criteria are summarised in table 1.

**Table 1 T1:** IVORY study withdrawal criteria

General	Cardiorespiratory arrest. Failure to attend two scheduled dosing appointments without adequate reason based on the PI assessment. Severe hypersensitivity reactions will preclude any further IMP administration. New seizure activity/coma. Severe lethargy or somnolence. Respiratory insufficiency requiring intubation. Pregnancy. Withdrawal of consent. PI discretion. Any serious adverse reaction (AR) or adverse reaction which is deemed by investigators to be severe AR. Any significant incidental finding on PET/CT scan clinical governance reports, which in the opinion of the PI, necessitates further investigation and management. Any medical history, clinically relevant abnormality or reason that is deemed by the PI to make the patient ineligible to continue the trial.
Cardiac	In patients without left bundle branch block (LBBB) QTc interval >500 ms OR change from baseline: QTcB >60 ms. In patients with LBBB if baseline corrected QT interval increases from <450 ms to >500 ms OR from 450 to 480 ms to >530 ms. (withdrawal of patients is to be based on an average QTc value of triplicate ECGs.) Patients who will be scheduled to undergo coronary artery bypass grafting. Patients who develop new-onset severe pulmonary oedema/new severe congestive heart failure, requiring high dose >240 mg over 24 hours intravenous furosemide during admission. Patients with symptomatic uncontrolled systolic BP <80 mm Hg and/or diastolic BP <50 mm Hg (after at least two repeat recordings), or severe hypertension (as defined by BP >180 mm Hg systolic BP or >120 mm Hg diastolic BP on at least two readings). Patients with sustained (>30 s) or symptomatic ventricular tachycardia and patients with ventricular fibrillation will be withdrawn.
Renal	Serum creatinine elevation >2× baseline screening visit (V1).
Liver	ALT ≥3× ULN and total bilirubin ≥2× ULN. ALT ≥5× ULN. ALT ≥3× ULN if associated with symptoms (new or worsening) believed to be related to hepatitis (such as fatigue, nausea, vomiting, right upper quadrant pain or tenderness or jaundice) or hypersensitivity (such as fever, rash or eosinophilia). Isolated ALT ≥3× ULN that persists for ≥4 weeks.

ALT, alanine transaminase; BP, blood pressure; IMP, investigational medical product; PI, principal investigator; ULN, upper limit normal.

### Study procedures

#### ^18^F-FDG scans

A General Electric Discovery 690 PET/CT scanner (Milwaukee, Wisconsin, USA) or equivalent scanner will be used for imaging. This will be performed using reproducible, validated methods for image acquisition, reconstruction and interpretation as recommended by the European Association of Nuclear Medicine for the conduct of clinical trials using ^18^F-FDG PET/CT.^40^ A dose of approximately 240 Mbq ^18^F-FDG will be injected through a peripheral venous cannula. The ascending aorta will be imaged 90 min after the ^18^F-FDG injection. Attenuation correction and non-contrast CT scans of the ascending aorta will initially be performed. This will be followed by a single-bed PET scan acquired in 3D list mode for 10 min, with the superior portion of the aortic arch as the upper anatomical landmark of the scan. Carotid artery imaging will be undertaken immediately after the PET/CT scans of the ascending aorta. A single-bed PET scan will be acquired in 3D list mode for 15 min, with the external auditory meatus as the upper anatomical landmark of the scan. PET data for the ascending aorta and carotids will be reconstructed using iterative 3D time-of-flight-ordered subset expectation maximisation with standard corrections applied±point-spread function modelling to reduce partial volume error. A CT carotid angiogram will also be carried out after the PET acquisition either in visit 2 or visit 15.

All scans will be anonymised. The anonymised scans will be analysed in batches of 20 by the research team. Second person checks will also be performed on a subset of these scans.

#### Lymphocyte subset assays

Lymphocyte subset assays will be performed at the Department of Clinical Immunology, CUH, and this will occur within 4 hours of sample collection. The clinical investigators and laboratory technicians will be blinded to treatment allocation.

Whole blood will be assessed by performing fluorescence-activated cell sorting (FACS) to measure the absolute and percentage values for lymphocyte subsets (Teffs, T helper 1, T helper 2, T helper 17 and T follicular helper cells) and Treg cells. Antibody reagent of 50 µL and 50 µL whole blood will be added directly to the BD Trucount tube. The lyophilized pellet in the tube dissolves, releasing a known number of fluorescent beads. During analysis, the absolute number (cells/µL) of positive cells in the sample can be determined by comparing cellular events to bead events. Figure 3 summarises the phenotypic characterisation of T lymphocyte subsets and the antibodies used in the FACS analysis.^23^

**Figure 3 F3:**
[figure not shown]
Lymphocyte subset analysis: A - Phenotypic characterisation of T cell subsets by flow cytometry; B -Antibodies used in fluorescence-activated cell sorting (FACS) analysis of T-cell subsets.

### Outcome measures and analysis

#### Image analysis

The table above lists the endpoints for this study (table 2). The primary endpoint in this study will be the change in vascular inflammation as measured by mean TBR_max_ in the index vessel on ^18^F-FDG PET/CT scans from baseline to follow-up. This will be calculated by demarcating a region of interest (ROI) including arterial wall and lumen on each axial slice of artery (ascending aorta and both carotid arteries) on the coregistered PET/CT scan and maximum standardised uptake values recorded. Subsequently, ROIs will be normalised by the blood pool ^18^F-FDG concentration in the superior vena cava or jugular vein (for carotids) and averaged to yield an arterial mean TBR_max_ as a quantitative measure of arterial tracer uptake. The ‘index vessel’ defined as the arterial territory with the highest mean TBR_max_ at baseline will be the primary outcome variable.^40^ The change in mean TBR_max_ will be calculated for each index vessel from baseline to follow-up and compared between the treatment groups.

**Table 2 T2:** IVORY study endpoint

Primary endpoints	Change in vascular inflammation (as measured by mean TBR_max_ in the index vessel) on ^18^F-FDG PET/CT from baseline to follow-up scans.
Secondary endpoints	Change in mean TBR_max_ in each arterial region individually restricted to those slices with TBR >1.6. Change in lymphocyte subsets between low-dose IL-2 and placebo. Change in percentage of Treg cells between low-dose IL-2 and placebo. The safety and tolerability of extended dosing of IL-2 in patients with ACS will be evaluated.
Exploratory endpoints	The change in serum cardiac biomarkers (eg, hsCRP, troponin, interleukin 6). Change in ejection fraction as measured on transthoracic echocardiograms. Change in phenotype and function of peripheral blood mononuclear cell subsets (such as B lymphocytes and natural killer cells) as assessed by flow cytometry, gene expression and in vitro activation and suppression assays.

ACS, acute coronary syndrome; ^18^F-FDG, 2-deoxy-2-[fluorine-18] fluoro-D-glucose; hsCRP, high-sensitivity C reactive protein; IL-2, interleukin 2; PET, positron emission tomography; TBR_max_, maximum target to background ratio; Treg cells, regulatory T cells.

Furthermore, an analysis of change from baseline in average TBR_max_ for active segments within the index vessel will be carried out, as previously described (figure 4).^35^ An active segment will be defined as a segment of a vessel with a TBR of ≥1.6. An analysis of the probability of a segment being active within the index vessel will also be calculated.

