**Figure 4 F4:**
[figure not shown]
Analysis methods used to quantify vascular inflammation in the index vessel. TBR, target to background ratio.

Change from baseline in average TBR_max_ will be analysed using analysis of covariance, fitting treatment as a fixed effect and including baseline value and ST-elevation status as covariates. Point estimates and corresponding 95% CIs will be constructed with p-values for the relevant comparisons of interest. All nominal p-values will be reported. Multiple testing across both analyses will be controlled using a gate-keeping approach. Multiple testing corrections will be carried out to obtain the p-values.

Average mean TBR_max_ data from the final imaging visit will be plotted to show the distribution from all segments from all index vessels within each treatment group. The difference between low-dose IL-2 and placebo will be calculated and tested using a non-parametric permutation test at an individual patient level.

The number of active segments and the total number of segments will be included in logistic regression analyses to model the probability of a segment being active. For baseline correction within each group, a model will be fitted with terms for treatment and visit. For placebo and baseline correction, a model will be fitted with treatment term, including the baseline proportion of active segments as a covariate.

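### Choosing the index vessel as the highest territory on the baseline scan biases the visit effect in the planned within-group active-segment model; the between-arm analyses are unaffected

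*Protocol article*

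**What the plan says.** All references are to the protocol article, section Outcome measures and analysis, Image analysis (including the paragraphs after Figure 4), unless stated.

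- **Selection.** Uptake is read "on each axial slice of artery (ascending aorta and both carotid arteries"), and the index vessel is "defined as the arterial territory with the highest mean TBR_max_ at baseline will be the primary outcome variable".
- **Change.** "The change in mean TBR_max_ will be calculated for each index vessel from baseline to follow-up and compared between the treatment groups". The scan that selects the vessel is therefore also the reference for its change.
- **Primary analysis.** An ANCOVA of change between arms, "fitting treatment as a fixed effect and including baseline value and ST-elevation status as covariates".
- **Active segments.** A segment is active at a TBR of 1.6 or more. "An analysis of the probability of a segment being active within the index vessel will also be calculated".
- **Within-group model.** In the logistic regression of active segments, "For baseline correction within each group, a model will be fitted with terms for treatment and visit".
- **Between-group model.** "For placebo and baseline correction, a model will be fitted with treatment term, including the baseline proportion of active segments as a covariate".

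The article does not mention regression to the mean and sets no limit on how the within-group result may be read.

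**The concern.** A vessel chosen because it read highest on one scan was, on average, read too high on that scan. When the same vessel is read again, the part of its lead that was measurement error does not recur. The expected change is therefore negative in unchanged patients, and the share of segments above a fixed threshold falls with it.

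A comparison of two randomised arms is protected, because the selection precedes dosing and follows the same rule in both. A comparison of follow-up with baseline inside the arms is not. The within-group logistic model makes that second comparison, on segments taken from the selected vessel. In a phase II trial whose hypothesis is a fall in vascular inflammation, a drop produced by the selection rule could be read as a response to IL-2.

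**Working it through.** **1. The plan's own figures** (Study population), with n = 2(1.960 + 0.842)²σ²/δ² per arm:

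- δ = 0.2, σ = 0.24: 2 × 7.849 × 0.0576/0.04 = 22.6, so 23, or 24 with the t distribution. The article says 24.
- δ = 0.125, σ = 0.166: 2 × 7.849 × 0.02756/0.01563 = 27.7, so 28, or 29 with the t distribution. Power at 30 per arm is 81.8%.
- 0.2/2.02 = 9.9% and 0.125/2.02 = 6.2%, in line with the stated 10% and 6%.

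The sample size is reproduced and is not in question.

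**2. Inputs for the selection effect**

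- From the article: total SD 0.24, reference value 2.02, three territories (two if the carotids count as one).
- Assumed: 0.166 is the SD of change and is all scan error, so the error SD per scan is 0.166/√2 = 0.117 and its variance 0.01378.
- Assumed and varied: the between-territory SD within a patient (σ_v), the share s of error variance common to all territories in one session, and any systematic level difference between territories.

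**3. Expected change with no effect.** If the territories have equal average uptake, only the unshared error variance σ_u² = 0.01378(1 − s) regresses:

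expected change = −c × σ_u² / √(σ_v² + σ_u²),

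where c is the expected maximum of independent standard normal values: 0.846 for three, 0.564 for two.

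| Territories | σ_v | s | Calculation | Expected change |
|---|---|---|---|---|
| 3 | 0 | 0 | 0.846 × 0.117 | −0.10 |
| 3 | 0.10 | 0 | 0.846 × 0.01378/0.1542 | −0.076 |
| 3 | 0.10 | 0.5 | 0.846 × 0.00689/0.1300 | −0.045 |
| 3 | 0.20 | 0.5 | 0.846 × 0.00689/0.2165 | −0.027 |
| 3 | 0.20 | 0.9 | 0.846 × 0.00138/0.2034 | −0.006 |
| 2 | 0 | 0 | 0.564 × 0.117 | −0.066 |

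Simulation agrees with these values. If one of three territories lies 0.3 above the others on average, simulation gives −0.036 to about 0. Averaged over all three territories without selection, the simulated change was 0.000 in every scenario tried.

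**4. Share of active segments**, the quantity that the within-group model uses. With an assumed segment SD of 0.25 and no effect:

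- σ_v = 0, s = 0: from 0.94 to 0.89; from 0.74 to 0.63 if average uptake is 0.3 lower.
- σ_v = 0.10, s = 0.5: from 0.94 to 0.92.
- One territory 0.3 higher, σ_v = 0.10, s = 0.5: 0.98 at both scans (a drop of 0.004).

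**5. The logistic model with treatment and visit terms**, 60 patients, 20 segments per vessel (assumed), standard errors clustered by patient, 300 no-effect trials per scenario. The visit term was nominally significant in:

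- 76% (σ_v = 0.10, s = 0) and 37% (σ_v = 0.10, s = 0.5), with no offset;
- 49% (σ_v = 0.15, s = 0) and 16% (σ_v = 0.15, s = 0.5), with the aorta 0.2 higher.

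With 300 trials the simulation error is up to √(0.25/300) = 2.9 points, so these rates show scale only.

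**6. The between-arm ANCOVA.** With no effect, 30 per arm, five scenarios of 4,000 trials: bias within 0.0005 and type I error 0.049 to 0.054, against 0.05 with a simulation error of √(0.05 × 0.95/4000) = 0.003.

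**The case against.** The strongest reply is that no between-arm result is biased. That stands: step 6 shows it for the ANCOVA, and the same reasoning covers the placebo- and baseline-corrected logistic model. A reader might infer from the selection rule that the primary endpoint is compromised. The document does not support that.

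A reader might also infer that both arms will show a false fall. That is not established. Only the direction of the expected bias is certain. All territories are imaged after one injection in one session, so errors may be largely shared. Treating the whole 0.166 as scan error leaves nothing for lasting differences in how patients change. Any real change after ACS would be mixed in.

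Simulated within-arm paired t tests on mean TBRmax at n = 30 show how far this varies. A nominally significant fall appeared in both arms in 90% of trials in the extreme case, 10% in a middle case and 0.2% when one territory dominated. The article plans no such test, so these rates cannot be charged to it.

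The within-group model names no treatment-by-visit interaction. As written, the artefact would sit in a visit effect common to both arms, not in IL-2 alone. This limits the harm but does not remove the bias: step 5 used that model.

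Finally, interpretive wording could be left to an analysis plan that is not shown, and it may already be there. But the article itself fixes the selection rule, the baseline and the within-group model, and together they produce the bias.

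**Conclusion.** The concern holds for one supplementary analysis. Followed as written, the plan builds a downward bias into the visit effect of the within-group active-segment model. The primary ANCOVA, the placebo-corrected model and the sample size are sound.

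The size cannot be fixed from the article. Under the assumptions in step 2 it runs from about 0 to −0.10 TBR units. The extreme is 0.10/0.2 = 50% of one design effect and 0.10/0.125 = 80% of the other, and it requires territories with identical true uptake and independent errors. A middle case of −0.045 is 0.045/0.2 = 22% and 0.045/0.125 = 36%. The bias is near zero if one territory is almost always the index vessel or if most scan error is shared.

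**What to change.** Before unblinding:

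1. Fit the within-group baseline-corrected active-segment model to all three territories. They are already imaged at both scans, and a secondary endpoint already uses each arterial region. Alternatively, keep it on the index vessel and report it as descriptive, subject to regression to the mean, without inferential p-values.
2. State that every efficacy claim rests on the between-arm contrast.

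The cost is wording. Pooling has two limits that should be stated. It removes the selection bias but not natural change after ACS, so a within-group fall remains non-causal. Its results also refer to different segments from those in the index-vessel placebo-corrected model.

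Optional: add index territory (aorta or carotid, fixed at baseline) to the ANCOVA. The territories are "normalised by the blood pool ^18^F-FDG concentration in the superior vena cava or jugular vein (for carotids"), so their levels may differ. Under assumed aorta–carotid offsets of 0.2 to 0.4, simulated residual SDs fell by amounts up to 0.1572 to 0.1492, that is 1 − (0.1492/0.1572)² = 10% of residual variance; with no offset the gain is nil. It costs one of 60 − 4 = 56 residual degrees of freedom. The ANCOVA is valid without it.

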**Figure 4 F4:**
[figure not shown]
Analysis methods used to quantify vascular inflammation in the index vessel. TBR, target to background ratio.

Change from baseline in average TBR_max_ will be analysed using analysis of covariance, fitting treatment as a fixed effect and including baseline value and ST-elevation status as covariates. Point estimates and corresponding 95% CIs will be constructed with p-values for the relevant comparisons of interest. All nominal p-values will be reported. Multiple testing across both analyses will be controlled using a gate-keeping approach. Multiple testing corrections will be carried out to obtain the p-values.

Average mean TBR_max_ data from the final imaging visit will be plotted to show the distribution from all segments from all index vessels within each treatment group. The difference between low-dose IL-2 and placebo will be calculated and tested using a non-parametric permutation test at an individual patient level.

The number of active segments and the total number of segments will be included in logistic regression analyses to model the probability of a segment being active. For baseline correction within each group, a model will be fitted with terms for treatment and visit. For placebo and baseline correction, a model will be fitted with treatment term, including the baseline proportion of active segments as a covariate.

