We plan to recruit 60 patients for the IVORY study. The sample size is based on an absolute difference of 0.2 in the primary endpoint (mean maximum target to background ratio (TBR_max_) in the index vessel) between placebo and active treatment at the end of the dosing period. This is equivalent to a 10% difference from a reference value of 2.02 and equivalent to the size effect observed after atheroprotective therapy.^35–37^ This is based on the results of previous studies that have reported less than a 10% difference in mean TBR_max_ in the index vessel between active treatment and placebo and failed to reduce cardiovascular outcomes.^34 39 41–43^

Assuming an SD of 0.24, 24 patients per arm, testing at two-sided 5% significance level, would provide 80% power. Therefore, a sample size of 30 completed patients per arm was selected to account for participant dropout and poor-quality scans deemed to be unsuitable for analysis (eg, because of motion artefact). This sample size of n=30 per group also allows the detection of a baseline-corrected 6% difference in TBRmax in the index vessel for the trial primary endpoint (mean 0.125, SD 0.166) between placebo and active treatment at the end of the treatment period, at 2-sided 5% significance level and 80% power.

The study opened on 26 August 2020. Thirty-three participants have completed the trial to date, and we expect recruitment to be completed by December 2023, after which the data analysis will commence.

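### The primary ANCOVA pools aortic and carotid index vessels without a territory term; the model is valid, but adding the term is a near-free gain in precision

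*Protocol article*

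**What the plan says.** All references are to the protocol article.

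- **Endpoint** (Outcome measures and analysis, Image analysis). The primary endpoint is the change in mean TBRmax in the index vessel. That vessel is the one of the ascending aorta and the two carotids with the highest mean TBRmax at baseline. Blood-pool normalisation uses the superior vena cava, or the jugular vein for carotids.
- **Acquisition** (Study procedures, 18F-FDG scans). The aorta is imaged 90 minutes after injection on a 10-minute bed. "Carotid artery imaging will be undertaken immediately after the PET/CT scans of the ascending aorta", on a 15-minute bed.
- **Primary model** (Image analysis, text after Figure 4). Change is analysed by ANCOVA, "fitting treatment as a fixed effect and including baseline value and ST-elevation status as covariates".
- **Randomisation** (Study protocol). The only stratification factor is ST-elevation status. The baseline scan follows randomisation but precedes dosing, and patients, trial team and image analysers are blinded.
- **Sample size** (Study population). For a difference of 0.2: "Assuming an SD of 0.24, 24 patients per arm, testing at two-sided 5% significance level, would provide 80% power". The target is 30 per arm, which is also said to detect a baseline-corrected difference of 0.125 with SD 0.166 at 80% power.
- **By-region analysis** (Table 2). The only one is a secondary endpoint, limited to slices with TBR above 1.6.

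**The concern.** Territory is neither balanced by the randomisation nor adjusted for in the model, although it is known for every patient with a baseline value. Suppose mean change at a given baseline differs between aortic and carotid index vessels. The difference then sits in the residual and widens the confidence interval. In the one trial that is run, an uneven split of territories between arms would also move the treatment estimate. With about 30 patients per arm and a target difference of 0.125, even a modest gain in precision is useful.

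**Working it through.** **1. Reproduce the plan's figures** (two-sample t-test, two-sided 5%).

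- Difference 0.2, SD 0.24, 24 per arm: power 80.7%. The stated 24 reproduces.
- Difference 0.125, SD 0.166, 30 per arm: power 81.8%. The stated 30 reproduces (29 would suffice).

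**2. What omitting the term does to validity.** The ANCOVA was simulated with and without a territory term (30 per arm, SD 0.166, 4,000 runs per setting, gaps up to 0.20, 20% or 50% carotid). Without the term, the treatment estimate was unbiased and type I error was 4.3% to 5.6% in every setting.

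**3. Can a territory gap arise in a within-vessel change?** A constant offset cancels in a plain change score for a fixed vessel. Here the vessel is selected as the baseline maximum and the model conditions on baseline. At equal baseline, a vessel from the lower territory lies further above its own mean and falls back more. A noisier territory is selected on error more often and also falls back more.

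This was simulated with no true change: one aorta and two carotids, between-patient SD 0.15, between-vessel SD within patient 0.15, one pooled baseline slope. All inputs are assumptions.

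| Aortic offset | Error SD, aorta / carotid | Adjusted gap in change | Residual variance explained |
|---|---|---|---|
| 0 | 0.12 / 0.12 | 0.00 | 0% |
| 0.1 | 0.12 / 0.12 | 0.03 | 1% |
| 0.1 | 0.10 / 0.15 | 0.07 | about 4% |
| 0.2 | 0.12 / 0.12 | 0.06 | about 4% |
| 0.2 | 0.10 / 0.15 | 0.10 | 9% |
| 0.3 | 0.10 / 0.15 | 0.14 | 13% |

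In the fifth row the SD of change is 0.170, close to the protocol's 0.166. Identical territories give no gap.

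**4. Effect on power.** Let f be the share of carotid index vessels and g the gap. The explained share is R² = f(1−f)g² / 0.166², and the residual SD becomes 0.166 × √(1−R²). With f = 0.5 and a difference of 0.125:

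| g | R² | Residual SD | Power, 24 per arm | Power, 30 per arm |
|---|---|---|---|---|
| 0 | 0% | 0.166 | 72% | 82% |
| 0.05 | 0.25 × 0.0025 / 0.02756 = 2% | 0.164 | 73% | 83% |
| 0.10 | 0.25 × 0.01 / 0.02756 = 9% | 0.158 | 76% | 85% |
| 0.15 | 0.25 × 0.0225 / 0.02756 = 20% | 0.148 | 82% | about 89% |

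Direct simulation at 30 per arm gave somewhat smaller gains. At g = 0.05 there was no material change. At g = 0.10 power went from 81.1% to 83.6% with half carotid, and from 79.9% to 80.9% with 20% carotid. At g = 0.15 it went from 81.0% to 88.3% and from 79.7% to 84.7%. If territory is not prognostic, power goes from 81.8% to 81.7%.

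**5. Chance imbalance.** The SD of the shift in the estimate is g × √(f(1−f) × 2/n). For g = 0.10, f = 0.5 and n = 30 this is 0.10 × √(0.5/30) = 0.013, so the 95% range is ±0.025, or 20% of 0.125. At 24 per arm it is ±0.028, or 23%. At g = 0.05 both halve. For comparison, the standard error of the treatment difference is 0.166 × √(2/30) = 0.043.

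**The case against.** The case for leaving the model alone is substantial.

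- **The model is valid as stated.** It adjusts for baseline and for the only stratification factor, it is unbiased and it holds its error rate. This stands.
- **No gap is documented.** The article gives no territory mix, no territory-specific SD and no difference in change. If 0.166 came from index-vessel data, it already contains the mix. This stands, so the gain can only be given as a range that includes zero.
- **The 50/50 mix is the most favourable assumption.** With 20% carotid and g = 0.10, R² is 0.16 × 0.01 / 0.02756 = 6% instead of 9%. Large gains need a gap of 0.15, more than the treatment effect itself. This stands.
- **Offsets cancel because each vessel is compared with itself, and a main-effect term cannot remove unequal noise.** This is only partly right. Selecting the maximum and conditioning on baseline can turn both into a difference in mean adjusted change (step 3).
- **Chance imbalance is already reflected in the confidence interval.** This is true on average over repeated trials. Adjustment still narrows the interval and removes the part of the shift that is due to territory.
- **The analysis plan, not shown, may add such a term.** That is possible, but the article states its covariate set, and the point concerns that statement.

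A reader might go further and infer that avoidable technical variance is known to remain, for example through larger partial-volume error in the carotids. The article does not support this. It mentions partial-volume error only as something that the reconstruction of both territories may reduce, and it does not compare the two.

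**Conclusion.** The point holds as a precision improvement, not as a fault in the primary analysis. The inferences that the primary estimate is biased, that type I error is inflated or that the trial is undersized are all contradicted by steps 1 and 2.

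What remains is that the stated covariate set leaves out a pre-dose, blindly read characteristic which the endpoint's own selection rule could make prognostic. With a 50/50 mix, SD 0.166 and 30 per arm, a gap of 0 to 0.10 TBR takes power for the 0.125 difference from about 82% to between 82% and 85%. At the upper end, the 95% confidence half-width falls from 0.086 to about 0.082. Larger gains need a gap above about 0.10. The mix and the gap are assumptions, and the gain is nil if the territories behave alike.

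**What to change.** Before unblinding, add index-vessel territory to the primary ANCOVA as a two-level covariate: ascending aorta versus carotid, left and right combined, fixed from the baseline scan. Also show the treatment estimate and its 95% confidence interval by territory, as description without a test, since the groups will be small. The secondary by-region endpoint does not serve this purpose, because it is restricted to slices above TBR 1.6.

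The cost is one or two sentences in the analysis plan, one degree of freedom (about 0.1 point of power if territory is not prognostic) and no new data. The timing matters: the same term added after unblinding would be post hoc.
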